**Methods:**

A pragmatic randomized controlled trial, single blinded, will include 2:1 allocation to the intervention group (IG) and the control group (CG). The IG will receive telephone assistance to quit smoking (including psychological and psychoeducational support, and pharmacological treatment advice if required) proactively for 12 months, and the CG will receive only brief advice after discharge. The sample size, calculated with an expected difference of 15 points on smoking abstinence between groups (IG, 20% and CG, 5%), α = 0.05, β = 0.10, and 20% loss, will be 334 participants (IG) and 176 participants (CG). Participants are adult smokers discharged from psychiatric units of five acute hospitals.

Measurements include dependent variables (self-reported 7-day point prevalence smoking abstinence (carbon monoxide verified), duration of abstinence, number of quit attempts, motivation, and self-efficacy to quit) and independent variables (age, sex, and psychiatric diagnoses). In data analysis, IG and CG data will be compared at 48 h and 1, 6, and 12 months post discharge. Multivariate logistic regression (odds ratio; 95% confidence interval) of dependent variables adjusted for potential confounding variables will be performed. The number needed to treat to achieve one abstinence outcome will be calculated. We will compare the abstinence rate of enrolled patients between groups.

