### Variables

#### Outcome measures

##### Primary outcome measure

Self-reported 7-day point prevalence smoking abstinence, biochemically verified with expired carbon monoxide (CO) measures, is the primary outcome. Seven days of abstinence has been chosen as a consumption measure [41]. This variable will be recorded in every call of the intervention (48 h, 1 week, 15 days, and 1, 3, 6, and 12 months post discharge). Abstinent subjects at 1, 6, and 12 months in either of both groups (IG or CG) will be invited to attend a consultation at their hospital to verify their abstinence through the detection of exhaled carbon monoxide. The abstinence rate between the IG and the CG will be compared at 1, 6, and 12 months. In each call, nicotine withdrawal symptoms will be assessed according to the scale proposed by Hughes and Hatsukami [42].

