#### Independent variables

Using a data collection form we will collect the following information:Sociodemographic data such as sex, age, occupation, and highest level of education attained.History and pattern of tobacco use, which will include information to obtain the Heavy Smoking Index as a measure of nicotine dependence self-reported by the participants [44, 45].General health data, such as self-perceived general health assessment by the question “how would you describe your health in a general way?”, and other medical conditions.Mental health data, such as diagnoses according to the DSM-5 groups of diagnostic criteria [46] and psychotropic treatment, will be obtained from participants’ clinical records by the researchers, whereas information about the number of emergency room visits, readmissions to psychiatric wards, and evaluation of mental distress measured using the 12-item version of the General Health Questionnaire (GHQ-12) [47, 48] will be self-reported by the participants.Variables of smoking cessation services reported by the participants, such as, if used, any other strategy for tobacco cessation, will be registered. It will also be recorded whether the patient has actively spoken with their psychiatrist, psychologist, nurse, or family doctor about their participation in the quitline, whether the professionals have agreed, and whether they have helped them, to assess the possible influence of these variables on the success (or failure) of the intervention.

Collected variables and their collection frequency are detailed in Fig. 1.

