For those patients who met the criteria, clinicians will invite them to participate and will deliver an informative leaflet of the study (Additional file 1). Informed consent will be requested within 24 h before discharge (see Fig. 2, recruiting process). Clinicians will register participants’ data in a software program that will be used for randomization and to transfer this information to 061 CatSalut Respon to contact the participants. All of this baseline information is registered in the software during the hospital stay. Finally, on the day of discharge the subjects are automatically assigned randomly to one of the two groups (IG or CG) by the software. The study is blinded to prevent professionals from the hospital, and patients, from knowing to which group they have been assigned.

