### Telephone-based intervention components

The intervention is based on cognitive-behavioral therapy. The intervention will include components based on Bandura’s social learning theory, social cognitive theory [49], and the transtheoretical model of change [43]. This theory allows evaluating the patient motivation phase and adapting the interventions according to each phase [27].

These components are included in the training curriculum aimed at 15 nurses from 061 CatSalut Respon who will deal with patients with mental disorders from the IG. The specific training will include the definition and description of the most common mental disorders, symptoms, usual treatments, warning signs, and management, as well as the peculiarities of the smoking cessation treatment in these patients (Table 1).

**Table 1 Tab1:** Components of the formative curriculum

• Mental disorders, symptomatology, and general treatment	
• Content, extension, and frequency of the proactive calls	
• Withdrawal syndrome assessment in the mental health context	
• Pharmacological recommendations about nicotine replacement therapy	
• Peculiarities of smoking cessation treatment in patients with mental disorders, alert signs, and management	
• Motivational intervention	
• Communication strategies	

Trained nurses will help those patients to identify their barriers and opportunities to achieve abstinence. They will also help them to set objectives, strategies to tackle “craving”, positive reinforcement toward progress, and increase their self-efficacy. If necessary, nurses will recommend NRT according to the protocol of a clinical guideline [28], as it is a medication that does not require medical prescription in Spain. Nurses will have a written protocol and an algorithm to deliver the intervention strategy according to each patient’s situation (Fig. 3). Nurses will recommend the patients inform their psychiatrist and/or psychologist that they are receiving this telephone-based intervention to quit smoking.

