**Fig. 3 Fig3:**
[figure not shown]
Strategy intervention in the intervention group. NRT nicotine replacement therapy

All patients in the intervention group will receive eight telephone calls during 1 year (48 h, 1 week, 15 days, and 1 , 3 , 6 , 9, and 12 months post discharge), regardless of whether they continue smoking or not. The intervention lasts for 12 months, unless the patient rejects to continue participating in the study. The intervention adapts its objectives depending on the smoking status of the patient in each call (see Fig. 3 in which the different strategies are explained according to the smoking status assessed in each call, whether he/she is abstinent or not, is willing to allocate a “D day”, takes NRT).

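### The blinding statement is contradicted by the intervention procedure: intervention patients, and any professional they inform, are not blinded during follow-up

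*Protocol article*

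**What the plan says.** The Procedure section describes automatic assignment by software on the day of discharge and then states: "The study is blinded to prevent professionals from the hospital, and patients, from knowing to which group they have been assigned". The Abstract describes the study as "A pragmatic randomized controlled trial, single blinded" and does not name the blinded party.

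The text after Fig. 3, under Telephone-based intervention components, says: "All patients in the intervention group will receive eight telephone calls during 1 year". The content is cognitive-behavioural, with quit-day planning and a nicotine replacement recommendation where needed. The same section adds: "Nurses will recommend the patients inform their psychiatrist and/or psychologist that they are receiving this telephone-based intervention to quit smoking".

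Under Independent variables the plan anticipates the result: "It will also be recorded whether the patient has actively spoken with their psychiatrist, psychologist, nurse, or family doctor about their participation in the quitline", and also "whether the professionals have agreed, and whether they have helped them". The stated purpose is to judge whether these factors influence success or failure.

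Control patients (Procedure) are called by nonclinical assistants at 48 h and at 1, 6 and 12 months, with brief advice in the first call only. Those who want to quit are pointed to an outpatient doctor, nurse or psychologist for help.

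Under Primary outcome measure, participants in either group who report abstinence at 1, 6 or 12 months "will be invited to attend a consultation at their hospital to verify their abstinence" by exhaled carbon monoxide (CO).

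**The concern.** The plan claims a protection that its own procedure removes for part of the trial. A patient who is counselled by a nurse for a year, and is advised to report it, knows what he or she is receiving. A clinician who is told knows the arm.

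Two things are at stake. The first is the risk-of-bias statement: if the results paper repeats that patients and hospital professionals were blinded, readers will credit the trial with protection it did not have. The primary outcome starts from self-report, so patients' knowledge of what they receive is relevant to it. The second is interpretation: a clinician who learns of the quitline may add support, and the plan expects this by recording it. The effect estimated is then that of the quitline together with the clinician involvement it prompts, and the report should say so.

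**Working it through.** The plan attaches no figure to blinding, so there is none to reproduce. The check sets the statements side by side and asks, party by party, what the procedure leaves masked.

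| Party | Claim (Procedure) | What the procedure does | Result |
|---|---|---|---|
| Intervention patients | Do not know group | Eight nurse calls with counselling; advised to tell their psychiatrist and/or psychologist that they receive the intervention | Not blinded |
| Professionals whom the patient informs | Do not know group, if they work at the hospital | Told by the patient; agreement and help are recorded | Not blinded once told |
| Professionals not informed | As above | No route to the arm is described | May remain unaware |
| Recruiting ward staff up to discharge | Do not know group | Baseline data entered during the stay; assignment automatic on the day of discharge | Allocation concealed |
| Control patients | Do not know group | Brief advice once, then neutral data-collection calls | May not know what the other arm receives; the leaflet is not shown |

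**Contrast between arms.** The intervention calls fall at 48 h, 1 week, 15 days and 1, 3, 6, 9 and 12 months, which makes 8. The control calls fall at 48 h and 1, 6 and 12 months, which makes 4. The callers differ (trained nurses against nonclinical assistants), and so does the content. Even without any disclosure, an intervention patient can hardly fail to see that cessation treatment is being given.

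**Number affected.** The intervention arm is planned at 334. The control arm is given as 176 (Abstract, Design) and as 167 (Sample size and randomization). The share of participants whose blinding is contradicted is therefore 334 / (334 + 176) = 334 / 510 = 65.5%, or 334 / (334 + 167) = 334 / 501 = 66.7%. Either way it is about two thirds.

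**The label.** The Procedure section names two blinded parties, patients and hospital professionals. The Abstract says single blinded. If both parties were blinded the label would fit poorly; if only one was, the Procedure sentence is too wide. Neither place says which.

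**Route to the primary outcome.** Smoking status is self-reported in the calls. In the intervention arm the nurses who deliver treatment make those calls. Only those who report abstinence are invited for CO testing. The test limits false claims of abstinence among those who attend; it does not make the self-report blinded.

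**The case against.** The best defence has five parts.

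- **Disclosure is recommended, not required.** This stands. Not every professional will learn the arm, so a reader who infers that the trial has no blinding of any kind goes beyond the text.
- **The professional told may not be a hospital professional.** This stands in part. The Procedure section refers to outpatient clinic staff after discharge, and the document does not show that they are the people the blinding sentence protects. A psychiatrist who does work at the hospital would be covered by that sentence and unblinded once told.
- **The sentence follows the description of assignment at discharge and may mean concealment.** Concealment up to that point is credible and worth keeping. But the sentence sets no time limit and includes patients, so as written it claims more.
- **In a pragmatic trial, clinician involvement prompted by the quitline belongs to its effect.** This stands, and is why the remedy is to describe the effect accurately rather than to change the advice. It does not make the blinding sentence true.
- **Control patients are also steered to clinicians.** This stands. Those who want to quit are told to seek help from outpatient staff. A reader might infer that some number of the 15 planned percentage points comes from extra clinician help in the intervention arm. The document gives neither a disclosure rate nor an effect of such help, and help may arise in both arms, so no figure can be supported.

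A reader might also infer that disclosure biases the CO readings. The plan does not say who takes them, and no route from knowing the group to an instrument reading is described. That remains conjecture.

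**Conclusion.** The blinding statement and the intervention procedure cannot both stand as written. Intervention patients are not blinded during follow-up, and neither is any professional they inform. This concerns the whole intervention arm, about two thirds of participants. The Abstract's label does not match the parties named under Procedure.

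The conclusion rests on the text alone and needs no assumption about how many patients disclose. It does not extend to saying that all masking is absent: ward staff can be unaware of allocation through recruitment and baseline entry, uninformed professionals can stay unaware, and control patients may not know what the other arm receives. The effect on the abstinence difference is unknown in size. The sample size and the analysis model are untouched. This is a point to correct before results are reported, because a plan should not claim a design property that it lacks.

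**What to change.** 1. Replace the blinding sentence under Procedure, and the label in the Abstract, with a statement of who is masked, to what and until when: allocation concealed from recruiting ward staff until automatic assignment at discharge; participants and treating professionals not blinded during follow-up.
2. Have the hospital staff who take CO readings work from an appointment list that does not show group. This is a cheap precaution, not a response to a demonstrated bias.
3. Make sure that the item on professional help under Independent variables is asked in both arms, in words that do not presuppose the quitline, for example whether any professional helped with smoking. The form and Fig. 1 are not shown, so part of this may already be in place. Report the item by arm.
4. Describe the estimated effect as that of the quitline including the clinician involvement it prompts.

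The advice that patients inform their clinicians is left as it is. The cost is two edits of protocol text, one list and at most one reworded question. The downside is that the stated blinding becomes less favourable.

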**Fig. 2 Fig2:**
[figure not shown]
Recruiting process

### Telephone-based intervention components

The intervention is based on cognitive-behavioral therapy. The intervention will include components based on Bandura’s social learning theory, social cognitive theory [49], and the transtheoretical model of change [43]. This theory allows evaluating the patient motivation phase and adapting the interventions according to each phase [27].

These components are included in the training curriculum aimed at 15 nurses from 061 CatSalut Respon who will deal with patients with mental disorders from the IG. The specific training will include the definition and description of the most common mental disorders, symptoms, usual treatments, warning signs, and management, as well as the peculiarities of the smoking cessation treatment in these patients (Table 1).

**Table 1 Tab1:** Components of the formative curriculum

• Mental disorders, symptomatology, and general treatment	
• Content, extension, and frequency of the proactive calls	
• Withdrawal syndrome assessment in the mental health context	
• Pharmacological recommendations about nicotine replacement therapy	
• Peculiarities of smoking cessation treatment in patients with mental disorders, alert signs, and management	
• Motivational intervention	
• Communication strategies	

Trained nurses will help those patients to identify their barriers and opportunities to achieve abstinence. They will also help them to set objectives, strategies to tackle “craving”, positive reinforcement toward progress, and increase their self-efficacy. If necessary, nurses will recommend NRT according to the protocol of a clinical guideline [28], as it is a medication that does not require medical prescription in Spain. Nurses will have a written protocol and an algorithm to deliver the intervention strategy according to each patient’s situation (Fig. 3). Nurses will recommend the patients inform their psychiatrist and/or psychologist that they are receiving this telephone-based intervention to quit smoking.

**Fig. 3 Fig3:**
[figure not shown]
Strategy intervention in the intervention group. NRT nicotine replacement therapy

All patients in the intervention group will receive eight telephone calls during 1 year (48 h, 1 week, 15 days, and 1 , 3 , 6 , 9, and 12 months post discharge), regardless of whether they continue smoking or not. The intervention lasts for 12 months, unless the patient rejects to continue participating in the study. The intervention adapts its objectives depending on the smoking status of the patient in each call (see Fig. 3 in which the different strategies are explained according to the smoking status assessed in each call, whether he/she is abstinent or not, is willing to allocate a “D day”, takes NRT).

### Data collection

A computer-specific application for the study will be designed for data recording and management, including randomization. The software will be created following the current standards of security, privacy, and confidentiality. All study researchers will have access to the application using a personal username and password. Clinicians from each center will only be able to register and have access to review information from patients from their own center. The 061 CatSalut Respon nurses will obtain data from patients registered in the five centers to do the telephone intervention. Collected data will be exclusively used to carry out the intervention (IG or CG), supervision, and evaluation. Patients will be informed about the application uses and purposes, the existence of their profile including their personal details, and the person responsible for their treatment, along with their access rights, rectification, cancellation, and opposition. Once the patient has given his/her consent, clinicians will input data from the basal interview into the application.

Once the study is completed, professionals from the hospitals and 061 CatSalut Respon will no longer have access to the database. The ICO is responsible for properly saving the files and its protection by encrypted secure systems, until its eventual destruction (5 years after study completion). The database will not identify patients in any way, creating an individual encrypted code. Data collected during the study will be included in a file registered by the Spanish Data Protection Agency.

The intervention and the computer application will be firstly piloted in the five participating centers for 1 month for its evaluation before starting the study, to assess the adequacy of the fieldwork circuit and make minor changes in the protocol, if necessary.

### Data analysis

The abstinence prevalence will be analyzed by groups taking into account sociodemographic determinants. Logistic regression analysis will be used to assess the effectiveness of the intervention (OR and 95% confidence interval) with regard to the CG, using the different dependent variables previously described (abstinence, reduction of the number of cigarettes, motivation, etc.). Thus, the IG and the CG will be compared in different moments of the follow-up. In addition to randomization, to warrant comparability, we will fit multivariate logistic models to adjust for potential confounding variables. All analyses will be carried out by “intention to treat”, to take into account possible losses during follow-up. We will also analyze resource use, such as the number of calls, satisfaction with the quitline, and type of treatment offered, among others.

### Ethical considerations

The intervention protocol has been approved by the Ethics Committee for Clinical Research (CEIC) from the Bellvitge Biomedical Research Institute (IDIBELL) (reference: PR276/16), as well as by the Ethics Committee of each of the five participating hospitals. The study protocol has been registered under ClinicalTrials.gov (NCT03230955, approved 24 July 2017).

At all times, requirements established by Law 14/2007, of 3rd July, on Biomedical Research will be met by researchers. The study will take place in compliance with the Declaration of Helsinki.

Smokers who meet the inclusion criteria will receive a brief explanation of the purpose of the study. They will also be given an information sheet and they will be asked to fill in the informed consent. The information will be protected according to the standards established by Spanish Law 15/1999 on the Protection of Personal Data.

The study termination criteria are the following (the first to be met): conclusion of the study procedures; if a patient explicitly states that he/she do not want to continue to participate in the study; and if a patient has repeatedly not been located in each of the off-tracking visits from both the intervention or control group during the 12 months of tracking.

## Discussion

Smoking has serious implications for people with severe mental illnesses, mainly in terms of quality of life and mortality but also in economic costs and marginalization. Hospital mental health units are an optimal setting to intervene and promote patient engagement in tobacco cessation treatment [21]. For this reason, it is necessary to offer and improve a variety of interventions to motivate and promote cessation among these patients.

Patients with mental health disorders are usually excluded from smoking cessation trials [20], and consequently there is scarce evidence for the effectiveness of quitlines in this population. As these patients usually have high comorbidity and high smoking dependence, they represent a complex population for smoking cessation intervention. They need more intensive counseling, pharmacological intervention, and longer follow-up support to achieve cessation [20], so there is a need to tailor these strategies to this population [50]. Only a few studies of quitline effectiveness have included mental health patients and, usually, quitline interventions have not been tailored to this population [51]. This is the first randomized trial to test a quitline intervention specifically tailored to the needs of mental health patients that incorporates a long-term follow-up of 1 year, since other studies have performed follow-up periods from 6 to 7 months [52] and with smaller samples [53].

The large sample, together with the long follow-up period, will allow us to perform other subgroup analyses in addition to assessing smoking cessation. The main expected outcome is an increased rate of CO-verified 7-day point prevalence abstinence in the intervention group, as compared with the control group. All smokers, regardless of their level of motivation to quit, will be eligible to participate. Analyses will consider covariates such as psychiatric diagnoses, use of other psychoactive substances, psychological distress, mental illness relapse and rehospitalization, and sociodemographic variables. Other relevant outcomes for comparison will include the level of motivation to quit, number of quit attempts, and level of psychological distress.

There are several potential limitations. In Catalonia, Spain, patients who have high motivation to quit smoking at the time of discharge from acute mental health hospitals are referred to a face-to-face intensive smoking cessation intervention with free pharmacotherapy for smoking cessation. These patients are excluded from our study and, therefore, our sample does not include patients with high motivation to quit smoking. Nonetheless, we will assess all patients who meet the study inclusion criteria and compare demographic, psychiatric, and tobacco use characteristics of those who accept or decline enrollment. Another limitation, derived from the long-term follow up design, is loss to follow-up that could bias follow-up findings. We will perform an attrition analysis comparing characteristics of those followed to those not followed at each time point. In addition, to preserve statistical power needed to observe a 15% difference in the quit rate between conditions, we have increased the baseline sample size to accommodate an anticipated 20% loss to follow-up at 12 months. To increase follow-up data collection, clinicians will collect contact telephone numbers for the participant and at least two family members or caregivers. There is potential for underreporting of smoking status at follow-up. Participants reporting nonsmoking status at follow-up receive a reminder and a clinic appointment to complete exhaled CO testing.

If effective, this intervention could be included in the Catalan Health System and regularly offered to mental health patients who smoke, no matter their motivation to quit. We need to offer a wide range of possibilities to intervene in smoking cessation in this population as their smoking prevalence has not decreased in the last decade (Additional file 2).
